#### Analysis

##### Infection rates

Infection rates will be analysed using Poisson regression with the infection counts as the dependent variable and the weekly number of patient days as the denominator. The key independent variable will be the intervention (yes/no). The intervention variable will switch from “no” to “yes” after the first full month of the intervention. The model will include a linear term for calendar time to control for any long-term pattern in infection rates. It will be a generalised linear mixed model (GLMM) with a random intercept for each hospital [29].

The characteristics of the hospital (e.g. size) will not be independent variables as these should remain roughly constant throughout the study. We will test the residuals of the model to look for autocorrelation over time and will check for influential observations. In a sensitivity analysis we will consider the possibility of a delayed intervention effect of up to one month. This is plausible because it may take time for the intervention to break the cycle of infection transmission.

The primary outcome will be a fixed effect meta-analysis of the estimated change in infection rates across the three infection types. We will use a forest plot to visually examine the variation in the change in infection rates. The combined mean will be considered statistically significant if the 95 % confidence limit does not include zero. The meta-analytic approach avoids using a combined infection rate, as this is questionable given the different drivers of infection. However, it will still give an overall estimate of the interventions impact on HAIs.

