## Discussion

### Limitations

This trial requires 11 participating hospitals. It could be difficult to recruit that number as it is very likely that some hospitals will decline or be unable to participate. This could be due to a number of reasons, e.g. disinterest in research, a lack of resources, a concern about negative impact on hospital budgets due to the need to implement change and increased product use associated with participation. This will be addressed by following an established recruitment process that provides clear information about what is required and a focus on fostering engagement and relationships with key decision makers at each site.

Once enrolled, willingness to participate may waiver for sites that are randomised to later trial commencement times. This will be addressed by maintaining communication with all sites and through ongoing monitoring of site context and engagement. The potential for fatigue related to participation, especially for the longer intervention phase sites, will be managed through frequent monitoring and engagement activities at the trial site.

We recognise some possible limitations in relation to the ‘opt-in’ nature of the recruitment process (i.e. that participating hospitals may be those most receptive to change and quality improvement). To mitigate this, we will as much as possible approach a range of eligible hospitals and will ensure we complete comprehensive context mapping at each site to fully understand the barriers and enablers that may have influenced the site’s decision to participate.

Other limitations could occur due to adverse events occurring at the staff, patient or hospital level during the trial. This could include outbreaks of HAIs, seasonal factors, organisational or policy changes. This will be mitigated by frequent monitoring of each site. Participating sites will agree to not implement changes that could impact the trial, e.g. cleaning policies or product use, without prior agreement from the study team. If there is a serious national epidemic during the trial the study will continue to collect data, but any planned changeovers to the intervention will be delayed until the epidemic has passed.

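### The primary 95% interval comes from Poisson models with only a hospital intercept, pooled as if the organisms were uncorrelated, so it is too narrow if infection counts vary over time within hospitals beyond Poisson

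*Protocol article*

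**What the plan says.** The Infection rates paragraph under Analysis fixes each step of the primary test.

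- Model family: "Infection rates will be analysed using Poisson regression with the infection counts as the dependent variable", with patient days as denominator.
- Time: "The model will include a linear term for calendar time to control for any long-term pattern in infection rates".
- Random effects: "It will be a generalised linear mixed model (GLMM) with a random intercept for each hospital". No other random effect is named.
- Pooling: "The primary outcome will be a fixed effect meta-analysis of the estimated change in infection rates across the three infection types".
- Decision rule: "The combined mean will be considered statistically significant if the 95 % confidence limit does not include zero".
- Diagnostics: "We will test the residuals of the model to look for autocorrelation over time and will check for influential observations". No change to the model or the standard error is tied to either check, and overdispersion is not among them.

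Two other statements bear on the variance. The same section justifies its delayed-effect sensitivity analysis by the time needed to interrupt transmission of infection. The Limitations section, on events that might disturb the trial, says "This could include outbreaks of HAIs" and adds seasonal factors and policy changes. Its answer is frequent monitoring of sites.

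**The concern.** A hospital intercept absorbs stable differences between hospitals, and a linear term absorbs a steady common trend. Neither absorbs a run of high months in one hospital. Each hospital switches once, so such a run falls mostly before or mostly after its switch and enters the intervention estimate. Poisson standard errors do not count that variation.

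The three organism estimates also share hospitals, calendar time and switch dates. A standard fixed effect meta-analysis gives them zero covariance. If a change in staffing, case mix or testing moves more than one organism, the pooled standard error is understated again.

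This interval is the trial's effectiveness verdict, and the infection reduction it describes feeds the cost-effectiveness analysis. The error runs towards declaring an effect that is not there.

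**Working it through.** **The plan's own figure.** The only related number is 86% power for a 20% reduction from 5 per 10,000 patient days. It can be neither reproduced nor refuted, because patient days per hospital are not stated and Fig. 1 is not shown. It is a separate matter and is not used below.

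**Inputs from the article.** 11 hospitals, 62 weeks, intervention lengths of 20 to 50 weeks, a combined rate of 5 per 10,000 patient days, and a two-sided 5% level.

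**Assumptions.** Starts after weeks 12, 15, …, 42 (equal 3-week steps); 3,000 patient days per hospital-week (range 1,400 to 4,200); organism rates of 1.0, 2.5 and 1.5 per 10,000. Expected infections: 11 × 62 × 3,000 × 0.0005 = 1,023. Extra variation is a log-normal hospital-by-4-week multiplier with SD 0, 0.3, 0.5 or 0.7 on the log rate.

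**What these SDs mean.** CV² = exp(SD²) − 1, so SD 0.3 is CV 0.31 and SD 0.5 is CV 0.53. For *C. difficile* the 4-week mean is 4 × 3,000 × 0.00025 = 3. Variance/mean = 1 + mean × CV², which is 1 + 3 × 0.094 = 1.28 at SD 0.3 and 1 + 3 × 0.284 = 1.85 at SD 0.5.

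**Procedure.** Three Poisson fits (hospital intercepts, linear time, intervention), pooled by inverse variance and rejected if |z| > 1.96, with no true effect. The log-normal column has 1,500 runs per row. The gamma columns use 400 beds (2,800 patient days per week) and gamma hospital-month multipliers. Entries are type I error in %.

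| Extra variation | Log-normal | Gamma, 2,000 runs | Gamma, 1,000 runs | Gamma, 400 runs |
|---|---|---|---|---|
| None | 5.2 | – | 4.5 | 5 |
| 0.3, independent over time and organisms | 6.3 | 7.0 | 5.5 | – |
| 0.3, autocorrelation 0.5 | 9.5 | – | 9.2 | – |
| 0.3, fully shared | – | – | 9.5 | 10.5 |
| 0.3, autocorrelation 0.5, half shared | 12.6 | – | – | – |
| 0.5, independent | 12.9 | 10.7 | 10.9 | 10 |
| 0.5, autocorrelation 0.5 | 17.9 | – | 15.7 | – |
| 0.5, fully shared | – | 19.9 | 20.1 | 23.5 |
| 0.5, autocorrelation 0.5, half shared | 22.9 | – | – | – |
| 0.5, autocorrelation 0.5, fully shared | 29.5 | – | – | – |
| 0.7, autocorrelation 0.5, half shared | 37.3 | – | – | – |

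The Monte Carlo standard error at 5% is 0.6 points with 1,500 runs and 1.1 with 400. At 23.5% with 400 runs it is 2.1.

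**Check by formula.** If r is the true SD of the pooled estimate divided by the mean reported SE, type I error is about 2[1 − Φ(1.96/r)]. In the log-normal set r was 1.08 to 1.25 at SD 0.3 and 1.29 to 1.83 at SD 0.5. At r = 1.25 the formula gives 11.7% (simulated 12.6%), at 1.29 it gives 12.9% (12.9%) and at 1.83 it gives 28.4% (29.5%).

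**Check with the stated random-intercept model.** On the same 500 data sets per scenario, a random-intercept GLMM and the fixed-intercept fit rejected in 2.8% and 3.0% (no extra variation), 12.6% and 11.8%, 16.6% and 16.2%, and 23.6% and 23.4%. The fixed-intercept shortcut does not drive the result.

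**Sensitivity to hospital size.** From 1,400 to 4,200 patient days per week, with autocorrelation 0.5 and half the variance shared, the range is 7.2% to 13.5% at SD 0.3 and 13.1% to 28.0% at SD 0.5.

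**Comparator.** A leave-one-hospital-out jackknife of the pooled estimate, with t on 10 degrees of freedom, gave 4.6% to 6.3% in every log-normal null scenario.

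**The case against.** The strongest objection is that the harm is conditional. The article gives no dispersion, hospital-month CV or cross-organism correlation, and it says only that outbreaks could occur. Under pure Poisson the planned rule holds its level. A reader might infer that the false-positive rate is known to be well above 5%; the documents do not support that. This stands.

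Second, an outbreak is usually of one organism, and the article keeps the organisms apart because their drivers differ. The independent rows are then the natural match, and at 0.3 they are mild (5.5% to 7.0%). Figures of 20% or more need CV 0.5 with full sharing, or comparable variation that is autocorrelated and shared. This also stands, except that an outbreak lasts beyond one period, so autocorrelation is hard to set aside, and it alone brings the 0.3 case to about 9%.

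Third, shared hospitals and dates do not by themselves correlate the estimates, and 11 clusters alone do no harm here: the row without extra variation is nominal on both counts. A reader might infer that the pooling is invalid in itself; it is not. It adds error only when variation is shared.

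Fourth, the plan includes autocorrelation and influence checks and a forest plot. They deserve credit, but none has a stated effect on the primary interval.

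Fifth, handling of overdispersion is often left to a statistical analysis plan. That would answer a complaint about missing detail. Here the article states the model, the pooling and the decision rule, and following them as written gives the narrow interval.

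**Conclusion.** The point holds in conditional form. The stated primary analysis has no place for hospital-by-time variation beyond Poisson, and the article's own account of transmission, outbreaks and season gives reason to expect some. Any such variation makes the 95% interval too narrow. Under the assumed sizes and reconstructed start dates, the excess over 5% ranges from slight (CV 0.3, independent) to serious (CV 0.5, where type I error is about 10% to 30%). The SD 0.7 row is an extreme case and not an estimate for this trial. Most of the excess comes from missing overdispersion and autocorrelation. At SD 0.5 with autocorrelation, sharing across organisms takes 17.9% to 29.5%. The direction is firm; the size rests on assumptions that the sponsor could check against its own surveillance data.

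**What to change.** Keep the organism-specific estimates and the pooled effect, and change the variance.

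1. Allow for overdispersion in each organism model, by a negative binomial model or a hospital-by-period random effect.
2. Base the primary interval and p-value for the pooled effect on a hospital-level variance that retains cross-organism covariance, for example a leave-one-hospital-out jackknife with t on 10 degrees of freedom, or on re-randomising the 11 start dates. Step 1 alone is not enough, since an independent hospital-by-period effect does not capture autocorrelation.
3. State what follows from the residual and influence checks.

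The cost is analysis work and an honest loss of precision, with no new data. With the assumed 3,000 patient days per week and start dates, simulated power for a 20% reduction under pure Poisson is 45.5% with the planned interval and 39.9% with the jackknife. With autocorrelation 0.5 and half the variance shared, the jackknife gives 27.5% at SD 0.3 and 18.9% at SD 0.5. The planned interval's apparent power there (45.9% and 47.9%) comes with false-positive rates of 12.6% and 22.9%. According to the Trial status section, randomisation was still to come when the article was submitted, so the change could be prespecified.

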#### Primary outcome—HAI rates

Whole hospital infection rates will be used as the primary outcome. This reflects the frequent movement of staff, patients and cleaners across hospitals wards and locations.

Hospitals will collect monthly data and then submit it at least bi-monthly to the project team. The numbers of SABs, CDIs and clinical isolates of VRE will be monitored, and rates calculated using algorithms based on nationally agreed definitions, as published by the Australian Commission on Safety and Quality in Health Care (ACSQHC) [25].

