#### Power calculation

Eleven hospitals with a pre-intervention infection rate (a combination of SAB, CDI and VRE infections) of 5 per 10,000 patient days will give us 86 % power to detect a 20 % post-intervention reduction in infection risk. This is based on a two-sided 5 % significance level, a within-hospital correlation in infection rates of 0.3 and the intervention timings shown in Fig. 1. The pre-intervention infection rate and within-hospital correlation were estimated using a dataset of over two million hospital admissions and infection data from nine Queensland hospitals [28]. The stepped-wedge sample size formula is from Hussey and Hughes [29]. We assumed no delay in the treatment effect for the sample size calculation, that is, rates decline as soon as the intervention begins.

To detect an increase in the secondary outcome (thoroughness of cleaning) from 82 to 87 % due to the intervention with a 92 % power requires only five hospitals with 40 observations per hospital per 4 weeks. This is based on the pilot data and recent studies [17, 22, 30, 31]. This secondary hypothesis requires far fewer hospitals because the outcome of cleaning failure is likely to be more common than HAIs (primary outcome), which are relatively rare.

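### The primary model counts the first full month of intervention as control time, while the power calculation assumes an immediate effect; any effect in that month pulls the estimate towards no effect

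*Protocol article*

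**What the plan says.** Four statements in the Protocol article bear on when a hospital starts to count as treated.

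- **Primary coding** (Analysis, Infection rates): a hospital's intervention variable changes from no to yes only "after the first full month of the intervention". The variable is binary, and the section names no transition period and no exclusion.
- **Power** (Power calculation): "We assumed no delay in the treatment effect for the sample size calculation, that is, rates decline as soon as the intervention begins".
- **Sensitivity analysis** (Infection rates): "In a sensitivity analysis we will consider the possibility of a delayed intervention effect of up to one month". The reason follows directly: "This is plausible because it may take time for the intervention to break the cycle of infection transmission". It is attached to the sensitivity analysis, not to the primary coding.
- **Time unit**: the model uses "the weekly number of patient days as the denominator", whereas the section on the primary outcome says "Hospitals will collect monthly data and then submit it at least bi-monthly to the project team".

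**The concern.** These statements do not describe one coherent primary analysis. The power calculation is for an effect that starts on the first day. The model withholds the treated label for at least a month and puts that month on the control side of the comparison. The sensitivity analysis then treats a delay of up to a month as a departure from the primary model, although the primary model already carries such a lag.

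If infections fall during the mislabelled month, the control rate is lowered by treated time and the estimated effect shrinks. In a stepped wedge adjusted for time, much of the information lies around each switch, and that is where the mislabelling falls. At stake is the primary effect estimate, and with it the number of infections prevented that drives the cost-effectiveness result.

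**Working it through.** **Inputs from the Protocol article.** 11 hospitals, 62 weeks and 20 to 50 weeks of intervention (Stepped-wedge design); a "pre-intervention infection rate (a combination of SAB, CDI and VRE infections) of 5 per 10,000 patient days", a 20% reduction, two-sided 5% level, within-hospital correlation 0.3 and 86% power (Power calculation); Poisson model with a hospital intercept and linear calendar time (Infection rates).

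**Assumptions.** Fig. 1 is not shown and is labelled an example, so the eleven starts are taken as evenly spaced: intervention lengths 50, 47, …, 20 weeks, that is, starts after weeks 12, 15, …, 42. Hospitals are of equal size. Fixed hospital intercepts stand in for the random intercept.

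**Step 1. The stated 86%.** It can be neither confirmed nor refuted, because patient days per hospital are not given. With the Hussey and Hughes variance and the assumed timings, power is about 22%, 46% and 75% at 200, 500 and 1,000 occupied beds per hospital, and 86% needs about 1,330 to 1,350. From here on, hospital size is set so that correct coding of an immediate effect gives exactly 86%. The power figures below are therefore relative to the protocol's own figure. The rate ratios do not depend on size.

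**Step 2. How much time is mislabelled.** Total intervention time is 11 × (50 + 20)/2 = 385 hospital-weeks. A 4-week lag mislabels 11 × 4 = 44 of them (11%). For the hospital with 20 weeks it is 4/20 = 20%.

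**Step 3. Expected estimate under an immediate effect.** Expected counts with rate ratio 0.80 from the first intervention week were fitted with the planned model.

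| Coding of the first 4 weeks | Expected rate ratio | Share of log effect kept | Power |
|---|---|---|---|
| Treated from the start | 0.800 | 100% | 86% |
| Control (as written) | 0.874 | ln 0.874 / ln 0.80 = 0.135/0.223 = 60% | about 45% |
| Excluded | 0.800 | 100% | about 77% |

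Check on the 45%: 86% power implies a standard error of 0.223/(1.96 + 1.08) = 0.0734. Then 0.135/0.0734 = 1.84, and Φ(1.84 − 1.96) = Φ(−0.12) ≈ 45%.

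With weekly period effects in place of linear time, the as-written ratio is 0.878. With no time term it is 0.824, but the protocol specifies a time term.

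**Step 4. Other onsets, same set-up** (the onset shapes are assumptions).

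| True onset of the 20% reduction | As written, 4-week lag | Switch at start | First 4 weeks excluded |
|---|---|---|---|
| Immediate | 0.874 | 0.800 | 0.800 |
| 2-week delay | 0.838 | 0.842 | 0.800 |
| Linear build-up over 4 weeks | 0.839 | 0.840 | 0.800 |
| 4-week delay | 0.800 | 0.881 | 0.800 |

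**Step 5. If a full month means a calendar month.** This reading is an assumption. A start within a month would add the rest of that month, and the lag could reach about 8 weeks. Under an immediate effect the expected ratio is then 0.943 and power about 12%.

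**Step 6. The sensitivity analysis.** Counted from the intervention start, a delay of one month is the primary coding again. Counted from the switch, it makes a lag of about two months. Neither is a zero-lag analysis, which is the case that was powered.

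**The case against.** The strongest reply is that a prespecified lag is a legitimate choice. Training takes place at the start of the intervention phase (Bundle components), so the bundle is still being introduced then, and the protocol itself gives a plausible reason for delay. An immediate effect in a power calculation is a planning simplification and does not bind the analysis model. This stands in part. With a full 4-week delay the written coding is unbiased and switching at the start is the worse choice (0.881). With a 2-week delay or a 4-week build-up the two are equally attenuated. What does not stand is counting the month as control: that is unbiased only if nothing at all happens in it.

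Two further points stand. A reader might infer that the sensitivity analysis simply duplicates the primary model. The text does not establish this, because a delay of up to one month could also mean shorter lags or a further lag after the switch. A reader might also take a lag of 8 weeks as planned. The first full month can equally be counted from each hospital's own start, and monthly collection does not rule out dated infections, so the 8-week figures are only the far end of a range.

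Lastly, a misplaced lag attenuates the estimate. It created no spurious benefit in any of the models tried.

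**Conclusion.** The point holds in conditional form. The primary coding and the power assumption conflict, and the analysis that was powered is not described. If any effect occurs in the first month, the primary estimate is pulled towards no effect: to about 0.87 for an immediate 20% reduction (power about 45% in place of 86%), to about 0.84 for a 2-week delay or 4-week build-up, and not at all for a full 4-week delay. Under the calendar-month reading the ratio could reach about 0.94.

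The direction was the same with linear, weekly or no time adjustment. The size rests on the assumed start times and the time term, and the power figures also rest on calibrating to 86%. Two stronger conclusions are not supported: that the primary estimate is certain to be biased, since the true onset is unknown, and that the stated 86% is wrong, since its inputs are not all given.

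**What to change.** In the primary model, define the first month after each hospital's start as a transition period of a fixed number of weeks, and exclude it instead of coding it as control. Put infection counts and patient days on one time unit, so that the period begins at the actual start date. Keep two sensitivity analyses, each with its lag counted from the intervention start: switch at the start, and a one-month lag. Restate the power on this basis.

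Exclusion returns 0.80 for any onset completed within the month. It does not fully remove attenuation if the effect builds up for longer.

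The cost is power: about 77% where no-lag coding would have 86% under an immediate effect, because 44 of 385 intervention hospital-weeks are dropped under the assumed timings. Sites would also need to supply infections and bed days on the same dated grid in place of monthly totals. The text change is a few sentences. It should be made before outcome data are seen, so that the choice of lag cannot be questioned later. According to Trial status, hospitals had not yet been randomised when the article was submitted.

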**Methods/design:**

The REACH study will use a stepped-wedge randomised controlled design to test the study intervention, an environmental cleaning bundle, in 11 Australian hospitals. All trial hospitals will receive the intervention and act as their own control, with analysis undertaken of the change within each hospital based on data collected in the control and intervention periods. Each site will be randomised to one of the 11 intervention timings with staggered commencement dates in 2016 and an intervention period between 20 and 50 weeks. All sites complete the trial at the same time in 2017. The inclusion criteria allow for a purposive sample of both public and private hospitals that have higher-risk patient populations for healthcare-associated infections (HAIs). The primary outcome (objective one) is the monthly number of *Staphylococcus aureus* bacteraemias (SABs), *Clostridium difficile* infections (CDIs) and vancomycin resistant enterococci (VRE) infections, per 10,000 bed days. Secondary outcomes for objective one include the thoroughness of hospital cleaning assessed using fluorescent marker technology, the bio-burden of frequent touch surfaces post cleaning and changes in staff knowledge and attitudes about environmental cleaning. A cost-effectiveness analysis will determine the second key outcome (objective two): the incremental cost-effectiveness ratio from implementation of the cleaning bundle.

The study uses the integrated Promoting Action on Research Implementation in Health Services (iPARIHS) framework to support the tailored implementation of the environmental cleaning bundle in each hospital.

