## Methods/design

### Study design

#### Stepped-wedge design

This is a randomised controlled trial using a cross-sectional stepped-wedge random allocation [12]. There will be sequential roll-out of an environmental cleaning bundle intervention to 11 Australian public and private hospitals over 62 weeks. Example trial timings are shown in Fig. 1.

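### The primary infection model adjusts for calendar time with a straight line only, so a shared seasonal or epidemic wave can leak into the intervention effect

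*Protocol article*

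**What the plan says.** The Infection rates part of the Analysis section specifies a Poisson model: "It will be a generalised linear mixed model (GLMM) with a random intercept for each hospital". On time it says: "The model will include a linear term for calendar time to control for any long-term pattern in infection rates". No seasonal or period term is stated. Exposure is coded with a lag: "The intervention variable will switch from “no” to “yes” after the first full month of the intervention". The model checks are: "We will test the residuals of the model to look for autocorrelation over time and will check for influential observations". The only sensitivity analysis stated for infection rates concerns an intervention effect delayed by up to one month. The model is fitted to three infection types, whose estimates are combined in a fixed effect meta-analysis.

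The design covers "11 Australian public and private hospitals over 62 weeks", with "an intervention period between 20 and 50 weeks".

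The Limitations section lists events that could disturb the trial: "This could include outbreaks of HAIs, seasonal factors, organisational or policy changes". The responses given are frequent site monitoring and site agreements not to change cleaning policy or products without the study team's consent. In a serious national epidemic data collection continues, but "any planned changeovers to the intervention will be delayed until the epidemic has passed". The article does not say how delayed changeovers would be coded or analysed.

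**The concern.** In this design the intervention is partly confounded with calendar time, because every hospital moves in the same direction, from control to intervention. The time adjustment therefore carries much of the weight in the primary estimate. A straight line can remove a steady drift but not a rise and fall. The trial lasts 62/52 = 1.19 annual cycles, too short for a seasonal pattern to average out. What remains of the wave after the line is removed can correlate with the roll-out, and the intervention coefficient absorbs that part. The article itself foresees variation of this kind and then fixes a model that cannot represent it. At stake is the primary rate ratio: a benefit could appear where there is none, or a real one could be masked, depending on when in the year the trial starts.

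**Working it through.** **What cannot be reproduced.** The stated 86% power cannot be checked, because the article gives no bed days and Fig. 1 is not shown. The check below does not depend on it.

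**Inputs from the article.** 11 hospitals; 62 weeks; intervention lengths of 20 to 50 weeks, so starts fall between week 62 − 50 = 12 and week 62 − 20 = 42; linear time; a one-month switch (taken as 4 weeks); a target rate ratio (RR) of 0.80.

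**Assumptions.** Equal 3-week steps (starts at weeks 12, 15, …, 42); hospitals of equal size; one pooled outcome; a wave common to all hospitals; hospital intercepts fitted as fixed effects in place of the random intercept. The article gives no seasonal amplitude, so a range is used.

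**Step 1: seasonal wave, no true effect.** Expected counts follow

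log rate = a_i + A·sin(2π(week + φ)/52),

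and the fitted model is

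log rate = a_i + β·X_it + γ·week.

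The table gives the range of exp(β) over 13 phases φ, four weeks apart.

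| Log amplitude A | Peak/trough = exp(2A) | RR, one-month switch | RR, immediate switch |
|---|---|---|---|
| 0.1 | 1.22 | 0.93 to 1.07 | 0.93 to 1.08 |
| 0.2 | 1.49 | 0.87 to 1.14 | 0.86 to 1.17 |
| 0.3 | 1.82 | 0.82 to 1.22 | 0.80 to 1.27 |

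With the one-month switch the worst-phase bias is about two thirds of the log amplitude. For A = 0.2, ln(0.873) = −0.136 and 0.136/0.2 = 0.68. The problem is not confined to one phase: at A = 0.2 the RR is more than 5% away from 1 at 10 of the 13 phases, with either coding.

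**Step 2: what a 20% bias requires.** With an immediate switch, RR 0.80 is reached at the worst phase when peak/trough is about 1.8. With the one-month switch, 1.9 gives 0.806 and 2.0 gives 0.792.

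**Step 3: masking.** With a true RR of 0.80, the one-month switch and peak/trough 1.5, the estimate ranges from 0.69 to 0.92 across phases.

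**Step 4: epidemic and delayed changeovers.** As an example, all rates are multiplied by 1.5 in weeks 20 to 30, with no true effect and linear time. Three starts (weeks 21, 24 and 27) fall in that window.

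| Handling of changeovers | RR, one-month switch | RR, immediate switch |
|---|---|---|
| No delay | 0.95 | 1.00 |
| Three affected sites wait, then start together | 0.91 | 0.87 |
| All remaining starts shift by 10 weeks | 0.98 | 0.95 |

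Onset was then varied over weeks 12 to 42, with multipliers of 1.5 or 2 lasting 8 or 12 weeks. Absolute bias was larger with delay for about 52% of onsets if the affected sites wait and start together. It was larger for 19 to 39% if all later sites shift.

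**Step 5: the alternatives.** For the waves in Step 1, 4-week period effects bring the RR to 0.995 to 1.005, and an annual sine/cosine pair brings it to 1.00. In the Step 4 example with the one-month switch, 4-week effects give 0.995 to 1.00. With an immediate switch and the three sites starting together, 4-week effects leave 0.96 and weekly effects give 1.00.

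**Step 6: price.** Assume 2,400 bed days per hospital per week, 5 infections per 10,000 bed days, RR 0.80 and an immediate switch. The standard error of log RR rises from 0.137 (linear) to 0.145 (4-week effects or sine/cosine), and 0.145/0.137 = 1.058. Power at that size is Φ(0.223/0.137 − 1.96) = 37% with linear time and Φ(0.223/0.145 − 1.96) = 34% with the richer terms.

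**The case against.** The strongest reply is that the sizes rest on assumption. The article reports no seasonal amplitude, Fig. 1 is missing, and the calculation lets all three infection types peak together, although the article stresses that their drivers differ. That is correct, and it is why the result is a range. If the types peak at different times, the biases may partly cancel in the meta-analysis.

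A second reply is that the residual autocorrelation check could reveal an unmodelled wave, and that the response may sit in an analysis plan that is not shown. This stands in part. The check could flag the portion of the wave left in the residuals, but not the portion already absorbed by the intervention term. The article attaches no action to the check. The linear term, moreover, is a stated choice and not an omitted detail.

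Third, weekly effects would be heavy for sparse counts in three separate models. That is fair, and the recommendation is therefore monthly or 4-week effects, with a sine/cosine fallback.

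A reader might also infer that delaying changeovers always favours the bundle. Step 4 shows that the direction depends on onset, exposure coding and rescheduling. Nor do the switch dates depend on the trial outcome: the stated trigger is a serious national epidemic, and the article does not say that it would involve any of the three infections. Finally, a reader might infer that the analysis differs from the model used for power. The article names the power formula but does not describe its time terms, so it does not support that claim.

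**Conclusion.** The point holds in a bounded form. A single linear term leaves the primary estimate open to material bias from a wave shared across hospitals, of a kind the article itself anticipates. Under the stated assumptions and the article's own switch rule, the bias reaches about 7% for a modest cycle (log amplitude 0.1) and 13 to 14% for a moderate one (0.2). At 0.3 the worst-phase RR is 0.82 or 1.22. A bias of the full 20% needs a peak/trough ratio of about 1.8 to 1.9 or slightly more at an unfavourable phase, and nothing in the article shows that such a cycle exists. If an epidemic delays changeovers and also raises these infection rates, the bias may grow or shrink.

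**What to change.** In the primary model for each infection type, replace the linear term with fixed monthly or 4-week period effects. Where counts of one type are too sparse for that, use linear time plus one annual sine/cosine pair, and state the rule for choosing before outcome data are seen. State how delayed changeovers are coded. If any occur, add a supporting analysis coded by the randomised start date.

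This needs a change of wording and no new data, since infection data are already collected monthly. The cost is a standard error about 5 to 6% larger and slightly lower power. Those figures come from one pooled outcome; the cost in three separate sparse models was not computed and could be higher.
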